### **Aim**

To investigate whether supplementation with high-dose vitamin D during third trimester of pregnancy has a favorable effect on the development of asthma and related disorders in the offspring.

### **Hypothesis**

High-dose vitamin D3 supplementation during third trimester of pregnancy will reduce the risk of developing asthma in the offspring.

### **Background**

Asthma, eczema and allergy are the most common chronic diseases among children and over the past 40 years, the incidence of these diseases has increased in industrialized countries through yet unknown factors in the environment.

Decreased levels of maternal vitamin D in pregnancy and thereby reduced fetal vitamin D levels in utero are among the early environmental exposures suspected to have an influence on the increased incidence of asthma in children.[1] Based on epidemiological studies, a high intake of vitamin D during pregnancy has been associated with protective effects on asthmatic symptoms in young children.[2,3] Preliminary results of a newer study indicates twice the risk of asthmatic symptoms in preschool children with low vitamin D levels at birth compared to children with a high level of vitamin D levels at birth.[4]

The results are consistent with several other studies, which suggest that the population in westernized countries have a reduced supply and level of vitamin D leading to an increased risk of various diseases. E.g., vitamin D levels in the fetus has been associated with the development of schizophrenia, diabetes mellitus and bone development.[5–7] Furthermore, high levels of vitamin D in adults appears to protect against a number of diseases, including bone diseases and cancer. [8–10]

The reason for these reduced levels of vitamin D may be found in the lifestyle of modern society. The majority of our vitamin D supply derives from sun exposure, and because of increasing awareness of harmful effects of sun exposure in relation to skin cancer, our supply of vitamin D has been markedly reduced. This is a recent development, which has led to the hypothesis that the current levels of vitamin D is too low according to the level for which we are genetically programmed.

Vitamin D level is however associated with and highly influenced by other factors as well. Therefore, it is necessary to conduct controlled, blinded studies on the effect of vitamin D supplementation to provide sufficient basis for future recommendations.

## **Method and trial procedure**

The women are recruited from the COPSAC2010 cohort; Local Ethics Committee (H-B-2008-093), Danish Data Protection Agency (2015-41-3696).

The study is a double-blinded, placebo-controlled, randomized parallel group design. 800 pregnant women will be randomized in a 1:1 ratio to intake of either high dose vitamin D supplementation or placebo according to one of the following regimes:

- 1) Placebo (+ guidance in recommended supplement of vitamin D (400 units daily)) or
- 2) High dose vitamin D supplement (2400units daily) (+ guidance in recommended supplement of vitamin D (400units daily))

The regimes are administered orally as 2 tablets daily.

Blinding and randomization are carried out by the Capital Region Pharmacy and stratified according to treatment group in the fish oil intervention study (ClinicalTrials.gov: NCT00798226). This allows for equal numbers receiving high dose vitamin D supplementation in both the fish oil active group and the fish oil placebo group.

The intervention is initiated at the beginning of the third trimester (pregnancy week 24) and continued until 1st visit to the COPSAC clinic after birth at week 1-2 postpartum. At the clinical visit in pregnancy week 24, the women will be provided with the intervention treatment and interviewed about current daily vitamin D intake and history of diseases likely to influence vitamin D levels. At pregnancy week 36 adherence to the regime will be assessed by interview at the COPSAC clinic. Furthermore, the women will be instructed to return the remaining tablets at the end of the intervention for evaluation of their compliance.

At pregnancy week 24 and 1st visit after birth a blood sample will be drawn from the mother in order to measure 25-OH-vitamin D, total calcium, parathyroid-hormone (PTH) and alkaline phosphatase.

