## **Inclusion criteria**

The study population consists of healthy pregnant women and their children participating in the COPSAC2010 cohort. Vitamin D supplements are administered during the third pregnancy trimester. The women will be included in the study independent of residence, age, race and social status during week 22-26 of pregnancy.

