## **Exclusion criteria**

Pregnant women are excluded from the trial, if they carry a disease leading to an increased risk of potential side effects from high-dose vitamin D supplementation: Endocrinologic disease in the form of calcium metabolic disorders, parathyroid disease, thyroid disorders or type 1 diabetes; Tuberculosis; Sarcoidosis or illness requiring chronic treatment with diuretics or heart medications, including calcium channel blockers or if they have a current intake of vitamin D supplements over the recommended dose.

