#### **Statistical analyses:**

The effect of high-dose Vitamin D3 supplementation on age at onset of persistent wheeze, lower respiratory infections, and eczema is analyzed by Cox proportional hazards regression, where p-values correspond to Wald tests. The children are retained in the model from birth until age of diagnosis, drop out, or age at their last clinic visit before the RCT was unblinded.

The effect of Vitamin D3 supplementation on the cross-sectional end-points asthma and allergic sensitization is analyzed by logistic regression, whereas the effect on number of wheezy episodes and upper respiratory infections is analyzed by a generalized estimating equation (GEE) Poisson regression model.

The effect on airway immunology is analyzed by calculating geometric mean ratios of each mediator in the high-dose Vitamin D3 vs. control group and by a principal component analysis (PCA) capturing the overall immunological trends in the data and their relation to the intervention analyzed by Wilcoxon rank sum test. Initially, the mediator levels were log-transformed. Prior to the PCA the variables were scaled to unit variance.

The primary analysis of persistent wheeze is presented crude and adjusted for sex, birth season, maternal Vitamin D level at randomization, and the n-3 LCPUFA RCT.

A significance level of 0.05 is used in all types of analyses.

Additional secondary endpoints:

The novel assessments introduced in the cohort resulted in additional secondary end-points:

Airway mucosal immune status

Description: Immune status measured in airway mucosal lining fluid at 4 weeks and 2 years of age (combined assessments by principal component analyses for each age point)

Systemic immune status

Description:

Main analysis: Immune status at 18 months measured in stimulated whole blood as cytokine release (combined assessments by principal component analyses)

Secondary analysis: Composition of immune cell subsets in whole blood at birth and at 18 months of age

Neurological development 0-3 years

Description:

Main analysis: Cognitive development assessed at 2½ years using the cognitive part of Bayley Scales of Infant and Toddler Development, third edition

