## STATISTICAL ANALYSIS PLAN – CURRENT STUDY

### Power calculation

Power analyses: The trial was powered according to the primary outcome of persistent wheeze/asthma. The statistical power of the nested RCT on neurodevelopment was calculated *post-hoc* based on the eligible children for such sub-analysis. A total of 551 children were included in the neurodevelopmental outcome assessment and 503 of these completed the BSID-III. The power calculation based on 503 children demonstrated over 80% power ( $\alpha=0.05$ , two-tailed) to detect a 5 points difference in the mean Cognitive Composite score (equivalent to 0.33 SD) between the two intervention groups.

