### Statistics

Probabilistic principal component analysis (pPCA) was used to generate principal *components* (PCs) for the milestone data assuming that missing values were missing at random. The PCs were used to assess if there was an overall effect on milestone development with subsequent analyses by linear regression analysis of individual milestones.

The effect of the high-dose vitamin D3 intervention on language development were assessed using Quasi Poisson regression models. The intervention's effect on Bayley-III cognitive composite score was assessed using linear regression models, while the effect on ASQ-3 general neurodevelopment was analyzed using Wilcoxon rank sum test.

The SDQ scores for total difficulties were divided into two groups: children with fewer and/or milder problems (values  $\leq$  median) and children with increased and more severe problems (values  $>$  median). The scores rating the functional impact of existing emotional and behavioral problems were grouped according to no or any impact. The effect of the high-dose vitamin D3 intervention on the SDQ scores was determined using logistic regression models.

All analyses were adjusted for maternal pre-intervention serum vitamin D3 levels, season of birth, sex, and n-3 LCPUFA RCT allocation.

Results are reported with 95% confidence intervals (CI), and 2-sided p-values. Missing data was treated as missing observations, except in the milestone pPCA.

The data processing was conducted using R version 3.5.2 (R core team 2018).

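### Women are randomised but children are analysed, multiple pregnancies are not excluded, and no method allows for co-twins: if twins are included, child-level standard errors are slightly too small

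*Supplement*

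**What the plan says.** **Randomisation.** The protocol, under Method and trial procedure, states that "800 pregnant women will be randomized in a 1:1 ratio to intake of either high dose vitamin D supplementation or placebo". Allocation is "stratified according to treatment group in the fish oil intervention study". No rule is given for multiple pregnancies.

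**Eligibility.** Under Inclusion criteria, "The study population consists of healthy pregnant women and their children participating in the" parent cohort, with no restriction to singletons. Under Exclusion criteria, "Pregnant women are excluded from the trial, if they carry a disease leading to an increased risk of potential side effects" of vitamin D, or if they already take more than the recommended dose. Multiple pregnancy is not mentioned in either section.

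**Analysis.** In the original statistical analysis plan (Statistical analyses), wheeze, eczema and lower respiratory infections are analysed by Cox regression with Wald tests: "The children are retained in the model from birth until age of diagnosis, drop out, or age at their last clinic visit" before unblinding. GEE Poisson regression is named only for counts of wheezy episodes and upper respiratory infections, and its cluster is not defined. The current-study plan's Summary of changes describes that plan as an addition to the original one, so these models still apply. The current-study plan (Statistics) adds quasi-Poisson models for language, logistic models for the SDQ and a Wilcoxon test for the ASQ-3. It also says the "effect on Bayley-III cognitive composite score was assessed using linear regression models". The adjustment set contains fixed covariates only.

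**Numbers.** Under Power calculation: "A total of 551 children were included in the neurodevelopmental outcome assessment", and "503 of these completed the BSID-III". The number of mothers behind these children is not given.

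**The concern.** Co-twins have the same mother, the same vitamin D allocation, the same fish oil allocation, the same baseline maternal vitamin D value and usually the same home. Their outcomes are likely to be positively correlated. Two positively correlated children in the same arm carry less information on the treatment contrast than two unrelated children do. A model that ignores this reports a standard error that is too small, a confidence interval that is too narrow and a p-value that is too low. The error runs towards false positives, and it would touch any child-level analysis in which twins appear and are correlated, including the primary wheeze analysis and the Bayley-III analysis. As the plan is written, a reader cannot tell how many independently randomised units lie behind 551 or 503 children.

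**Working it through.** **1. The plan's own power figure.** Inputs from Power calculation: 503 children, a difference of 5 points, 0.33 SD (so SD about 15), two-sided alpha 0.05. Equal arms of 251.5 are assumed.

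- SE = 15 × √(2/251.5) = 1.338
- 5/1.338 = 3.738; 3.738 − 1.960 = 1.778; power = Φ(1.778) = 0.962

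The plan says over 80%, which is met. This calculation treats all 503 children as independent.

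**2. Variance inflation for twins.** Let p be the share of pregnancies that are twin pregnancies and ρ the within-pair correlation. Both are assumptions. With clusters of size m = 1 or 2 and one allocation per cluster:

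DE = Σm(1 + (m − 1)ρ) / Σm = 1 + 2pρ/(1 + p)

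The correct SE is √DE times the reported one. The true error of a nominal 5% test is 2 × (1 − Φ(1.960/√DE)). Power for the 5-point difference uses 503/DE children.

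| p | ρ | DE | Correct SE vs reported | True error | 503/DE | Power |
|---|---|---|---|---|---|---|
| 1% | 0.3 | 1.006 | +0.3% | 5.07% | 500 | 0.961 |
| 2% | 0.6 | 1.024 | +1.2% | 5.3% | 491 | 0.959 |
| 4% | 0.8 | 1.062 | +3.0% | 5.71% | 474 | 0.952 |

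In the last row the nominal 95% interval covers 94.3%. As an extreme, p = 10% and ρ = 1.0 gives DE 1.182, SE +8.7%, true error 7.1% and power 0.930.

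**3. Shared versus separate allocation.** The formula applies only when both children carry the same allocation. Data sets of 503 children were simulated under no effect, with ρ = 0.7 and 20,000 runs (Monte Carlo error about √(0.05 × 0.95/20,000) = 0.0015).

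| Mothers with two children | Rejection rate, shared allocation | Rejection rate, separate allocation |
|---|---|---|
| 2% | 0.051 | 0.048 |
| 5% | 0.063 | 0.049 |
| 20% | 0.077 | 0.048 |

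The 0.063 lies above the formula's 0.058. A repeat with 60,000 runs gave 0.059, so the excess is mostly simulation noise. When two siblings are randomised separately, they fall in the same arm about as often as in opposite arms, and their covariance averages to about zero in the difference between arms.

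**4. Does clustering repair it?** In a simulation with about 500 children, variance clustered by mother brought the type I error back to about 5%, with a mean change in SE of +1% to +3%.

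**The case against.** Three objections carry weight.

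- **No section reports a twin.** The trial is nested in a parent cohort whose own eligibility rules are not shown, and the trial's criteria are additions aimed mainly at vitamin D safety. Their silence does not prove that twins entered. This stands, and it makes the point conditional. A reader might infer that every child-level interval in the trial is too narrow; the documents do not support that. With no twins there is no error, and for an outcome with ρ near zero there is almost none.
- **Repeat pregnancies are different.** A reader might extend the argument to any siblings who share a mother. That fails for separately randomised pregnancies, as step 3 shows. It would hold only if a woman kept her first allocation, and the documents say neither that nor that a woman could enrol twice.
- **The effect is small.** This stands too. At 1% to 4% twins no power conclusion changes. With nearly all clusters of size one, a robust variance barely moves and in a single data set can come out slightly smaller.

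None of this fills the gap. A plan that randomises mothers and analyses children needs to say how co-twins are handled.

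**Conclusion.** The point holds in conditional form. The randomised and analysed units differ, the criteria shown admit multiple pregnancies, and no analysis allows for co-twins. If twins were included, reported standard errors are slightly too small. The size in step 2 rests on assumed twin shares and correlations, not on figures in the documents, and on one correlation range being used for outcomes as different as wheeze and cognitive score. The matter is minor in magnitude, but where it acts it favours false positives, and it is easily corrected.

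**What to change.** In the Statistical analyses section of the original plan and the Statistics section of the current-study plan:

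- State whether twins were included, and report the numbers of women and of children per arm for each analysis.
- Use cluster-robust (sandwich) variance by mother in the Cox, linear, quasi-Poisson and logistic models.
- Define the GEE clustering so that it accounts for the mother as well as for repeated records on one child.
- For the Wilcoxon tests, use a clustered version or one randomly chosen child per mother.

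The cost is a short addition to the plan and a cluster option in the existing R code, with no new data. If twins are present, intervals widen by about 0.3% to 3% on average under the assumptions above. If there are none, a sentence saying so closes the matter and the clustered variance changes essentially nothing.

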## **Inclusion criteria**

The study population consists of healthy pregnant women and their children participating in the COPSAC2010 cohort. Vitamin D supplements are administered during the third pregnancy trimester. The women will be included in the study independent of residence, age, race and social status during week 22-26 of pregnancy.

## **Exclusion criteria**

Pregnant women are excluded from the trial, if they carry a disease leading to an increased risk of potential side effects from high-dose vitamin D supplementation: Endocrinologic disease in the form of calcium metabolic disorders, parathyroid disease, thyroid disorders or type 1 diabetes; Tuberculosis; Sarcoidosis or illness requiring chronic treatment with diuretics or heart medications, including calcium channel blockers or if they have a current intake of vitamin D supplements over the recommended dose.

## **Risks and disadvantages:**

Known potential adverse effects of vitamin D intoxication is hypercalcemia and accompanying symptoms such as loss of appetite, nausea, vomiting, weight loss, headache, lethargy, fatigue, confusion and renal impairment. These side effects are not found by the administration of vitamin D

in physiological doses. Vitamin D intoxication occurs only by the intake of very high doses of Vitamin D (4 times higher doses than administered in our study). In order to avoid administering vitamin D supplements to women with a high initial level, women with an intake above the recommended dose in the previous 6 months are excluded. Expected disadvantages related to blood sample procedures and are temporary in nature without the risk of permanent injury.

### **Ethical aspects**

Oral vitamin D supplement has been shown to be safe and non-toxic in many randomized trials, including studies involving pregnant women. The risk of adverse effects in the pregnant woman or the fetus is suspected to be minimal. Based on the previous studies, it is expected that a large proportion of the participating women will have a daily low Vitamin D level, and thereby vitamin D supplementation to these women will be a health benefit. The control group receive recommended dose of vitamin D, and ethical problems in relation to sufficient treatment of the control group is thereby not a problem.

We believe that the study as outlined above is ethically acceptable and randomized trials of vitamin D supplements are necessary for future recommendations of vitamin D intake.

### **Study Description**

#### **Brief Summary:**

The aim of this study is to prevent asthma symptoms (recurrent wheeze) in childhood by supplementation with high dose vitamin D to the mother during pregnancy. Participants are mothers and children of the ABC (Asthma Begins in Childhood) cohort. Mothers are recruited during pregnancy and receive daily supplement with 2400 IU of Vitamin D3 or placebo from week 24 of gestation to 1 week after delivery. In addition all mothers are advised to take the recommended dose of 400 IU vitamin D daily. The mothers in ABC also participate in an interventional trial with fish oil supplementation, and the vitamin D randomization is stratified by fish oil treatment group. The child is followed with acute and planned visits at the research unit, and wheeze is diagnosed according to predefined algorithms.

#### **Arms and interventions:**

Active Comparator: Vitamin D

Dietary supplement: 2400 IU Vitamin D3 (2 tablets of 1200 IU) from week 24 of gestation to 1 week after delivery.

Dietary Supplement: Cholecalciferol D3 2 tablets of 1200 IU daily from week 24 of gestation to 1 week after delivery. Vitamin D from Camette, Denmark

Placebo Comparator: Placebo

Placebo: 2 placebo tablets with no active substance, identical to the active tablets, from week 24 of gestation to 1 week after delivery

Placebo tablet: 2 tablets containing no active substance. Placebo tablets from Camette, Denmark

#### **Outcome Measures**

##### **Primary Outcome Measure:**

1. Persistent wheeze

Age at onset of persistent wheeze diagnosed according to predefined algorithm of recurrent troublesome lung

symptoms, response to treatment and relapse after withdrawal of treatment

[Time Frame: 0 to 3 years of age]

##### **Secondary Outcome Measure:**

2. Infections

Main analysis:

- Number of lower respiratory tract infections registered in daily diaries

Secondary analyses:

- Acute otitis media
- Number of upper respiratory tract infections
- Number of other infections
- Total number of infections

[Time Frame: 0 to 3 years of age]

### 3. Allergic sensitization

Allergic sensitization at 6 and/or 18 months assessed by skin prick test and specific IgE in blood

[Time Frame: 6 and 18 months of age]

### 4. Eczema

Age at onset of eczema diagnosed prospectively by research doctors according to predefined algorithm based upon

Hanifin and Rajka criteria

[Time Frame: 0 to 3 years of age]

### 5. Mothers levels of 25-OH-Vitamin D, PTH, Calcium, alkaline phosphatase

[Time Frame: 1 week after delivery]

### 6. Growth

[Time Frame: 0 to 3 years of age]

### 7. Asthma exacerbations

Age at onset of severe asthma exacerbation diagnosed by predefined criteria of acute severe asthma requiring oral/

high dose inhaled steroids or acute hospital contact

[Time Frame: 0 to 3 years of age]

### 8. Neurological development

Main analysis:

- Cognitive development assessed at 2½ years using the cognitive part of Bayley Scales of Infant and Toddler development, third edition

Secondary analyses:

- Milestone development monitored prospectively by the parents using a registration form based on The Denver Development Index and WHO milestones registration (combined assessment by principal component analysis)

- Language development assessed at 1 and 2 years of age with the Danish version of The MacArthur Bates Communicative Developmental Inventory (CDI)

- The child's general development (language, fine and gross motor, social and problem solving) at 3 years of age assessed with Ages and stages Questioner, third edition (ASQ-3)

[Time Frame: 0-3 years]

### 9. Growth

Main analysis:

- Body composition (fat mass and bone mineral density) assessed by DEXA scan at 3 years of age

Secondary analysis

- Development of BMI from birth to 3 years assessed longitudinally in the research clinic  
[Time Frame: 0-3 years]

